### Participant timeline

The planned duration of the study is 24 months, starting in the summer of 2024. Patients will be enrolled consecutively during the first 12 months. The intervention will be administered daily during the ICU stay, as long as the patient's medical condition permits, and will end at ICU discharge or a maximum of 28 days after randomization, whichever occurs first. All participants will receive standard ICU care. Follow-up visits will be performed three and 12 months after ICU discharge (Fig. 5).

**Fig. 5 Fig5:**
[figure not shown]
Timeline of study procedures. ICU, intensive care unit; TAU, treatment as usual; RGS-ICU, Rehabilitation Gaming System for Intensive Care Units

### Sample size and power calculation

Sample size is based on the test of equality of two independent means for the primary outcome (objective cognition 12 months after ICU discharge) calculated using G-Power v3.1.9.7 software [48, 49]. Based on data from a randomized clinical pilot using the ENRIC platform [13], an eta squared effect size of 0.14 is anticipated. With a statistical power of 0.8 and a two-sided alpha level of 0.05, a minimum sample of 26 participants per group is needed to detect a Cohen's d effect size of 0.8 (total *n* = 52). Considering a dropout rate of 50% (15% during the ICU stay and 35% after ICU discharge), the minimum recruited sample needed for this RCT is 78 participants (*n* = 39 per group). Thus, at least 80 patients with critical illness (*n* = 40 per group) will be recruited, half of them in each participating hospital. However, since this RCT takes place in the ICU, it is to be expected that some dropouts will occur for reasons unrelated to the study itself (e.g., changes in health status that make continued participation inadvisable, mortality in the ICU, transfer to another ICU or withdrawal of consent previously given by an authorized representative). Thus, to maintain a sample size with sufficient power, these participants, estimated at 15%, will be replaced by new enrolments in a 1:1 ratio.

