## Discussion

This is a two-arm, parallel-group, superiority RCT aimed at evaluating the efficacy and safety of receiving early cognitive stimulation and relaxation as an adjunct to standard ICU care compared to receiving standard ICU care alone. This trial responds to the need to humanize intensive care [64], a new paradigm of human-centered ICU care that aims to actively involve patients in their recovery process, as intended by the RGS-ICU intervention.

This RCT builds on previous PoC and clinical pilots that demonstrated that neuropsychological e-health interventions based on VR techniques, whether immersive or not, used as an adjunct to standard ICU care, in addition to being safe for patients with critical illness [19], can help reduce anxiety during the ICU stay [20], as well as improve working memory performance after ICU discharge [13]. However, these studies were limited by methodological issues such as single-center designs, small sample sizes (n ≤ 21 subjects per group), heterogeneous diagnoses, interventions that included cognitive but not relaxation protocols, and absence of assessment of variables such as experienced comfort, subjective cognition, functionality and HRQoL.

In an attempt to overcome these limitations, the RGS-ICU trial has been designed, whose main strengths include a multicenter design, strict inclusion/exclusion criteria, an adequately powered sample size to test the primary outcome (i.e., objective cognition 12 months after ICU discharge), the use of an enhanced and optimized e-health intervention combining cognitive protocols to stimulate the brain with relaxation videos to promote stress and anxiety reduction, and the administration of a full neuropsychological battery to characterize the cognitive, mental health, functional and HRQoL profile of survivors of critical illness. This trial will also benefit from monitoring patients' physiological parameters as part of standard ICU care to ensure the safety of the intervention and that it is adapted to their mental status and mobility level in real time. In contrast, its open design is a limitation that will be compensated by blinding the data analysis by an independent statistician. Following SPIRIT guidelines for reporting study protocols [22], the sample size has been calculated for the primary outcome, so the study may be underpowered for test other outcomes. The use of self-reported measures to assess mental health may also be a limitation of the study.

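### The step from 52 evaluable to 78 recruited does not follow from a 50% dropout rate (it would be 104), and the 15% ICU loss is used twice; whether the planned 80 gives 0.80 power depends on an unstated denominator

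*Protocol article*

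**What the plan says.** All the figures are in the protocol article, Sample size and power calculation.

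- Basis: "Sample size is based on the test of equality of two independent means for the primary outcome (objective cognition 12 months after ICU discharge").
- Evaluable number, at 80% power and a 5% two-sided test: "a minimum sample of 26 participants per group is needed to detect a Cohen's d effect size of 0.8", which makes 52 in total. The effect comes from a pilot: "an eta squared effect size of 0.14 is anticipated".
- Allowance for loss: "Considering a dropout rate of 50% (15% during the ICU stay and 35% after ICU discharge").
- Number to recruit, as the plan derives it from that allowance: "the minimum recruited sample needed for this RCT is 78 participants", or 39 per group, raised to at least 80 (40 per group).
- Replacement: patients lost for ICU-related reasons are not simply absorbed; "these participants, estimated at 15%, will be replaced by new enrolments in a 1:1 ratio", with the declared aim of keeping sufficient power.

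The Discussion then counts among the trial's strengths "an adequately powered sample size to test the primary outcome".

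**The concern.** If half of those recruited are lost, 78 recruits leave 39 completers, not the 52 that the power calculation requires. The 78 comes from adding 50% to the evaluable number, when the evaluable number should have been divided by the fraction expected to remain.

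The paragraph also deals with the 15% ICU loss in two ways that do not fit together. It is part of the 50% used to reach 78, and it is then removed again by replacing those patients. A reader cannot tell whether 80 is the number randomised or the number still in the trial at ICU discharge, or what the 35% is a percentage of.

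This paragraph is the only justification of the sample size for the primary outcome, and the adequacy claim in the Discussion rests on it.

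**Working it through.** **Inputs** (Sample size and power calculation): d = 0.8, two-sided alpha 0.05, power 0.80, two independent means; losses 15% in the ICU and 35% after discharge, summed to 50%; recruited 78, raised to 80; the 15% replaced 1:1. The 1:1 allocation is from Trial design.

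**1. The evaluable number reproduces.** Eta squared 0.14 corresponds to d = 2 × √(0.14/0.86) = 0.807, consistent with 0.8. The two-sample t-test (noncentral t) at d = 0.8 needs 25.52, so 26 per group and 52 in total. Power at 26 per group is 0.807.

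**2. The inflation does not reproduce.**
- Plan's figure: 52 × (1 + 0.5) = 78.
- Correct form for 50% loss: 52/(1 − 0.5) = 104.
- Check: 78 × 0.5 = 39 completers.

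**3. The denominator of the 35%.** The sum 15% + 35% = 50% is exact only if both are shares of the same recruited total. If the 35% applied to those discharged, total loss would be 1 − 0.85 × 0.65 = 0.4475, about 45%. On the common denominator, the loss among those discharged is 0.35/0.85 = 41%.

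**4. What the planned numbers deliver** (power at d = 0.8, two-sided 0.05, patients with 12-month data):

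| Reading | Completers | Per arm | Power |
|---|---|---|---|
| 80 retained at ICU discharge after replacement, 35% of those lost | 80 × 0.65 = 52 | 26 | 0.81 |
| 78 retained, 35% of those lost | 78 × 0.65 = 50.7 | 25 to 25.35 | 0.79 to 0.80 |
| 80 retained after replacement, 35% a share of all randomised | 80 × (1 − 0.35/0.85) = 47 | 23.5 | 0.77 |
| 80 randomised, no replacement, 15% then 35% of the remainder lost | 80 × 0.85 × 0.65 = 44 | 22 | 0.74 |
| 80 randomised, no replacement, 50% lost | 80 × 0.5 = 40 | 20 | 0.69 |

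**5. Number randomised implied by replacement.** To have 80 still in the trial at ICU discharge with 15% lost before then: 80/0.85 = 94.1, so 95. If the 12 lost (15% of 80) are replaced only once, the total is 80 + 12 = 92. Replacements also lost at 15% then leave 92 × 0.85 = 78.2 at discharge and 78.2 × 0.65 = 50.8 completers, power 0.80.

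**6. Number needed on the common-denominator reading.** 52/0.5 = 104 randomised, of whom 104 × 0.85 = 88.4 remain at ICU discharge.

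**The case against.** The strongest defence is that the plan does not leave the ICU losses uncorrected. Replacement is stated, and so is its purpose. Once those patients are replaced, only the post-discharge loss reduces the sample, a share of those discharged is a natural meaning of the 35%, and 52/0.65 is exactly 80. The target of 80 is also worded as a floor, so randomising 95 would not breach it.

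Most of this stands. A reader might infer from the faulty inflation that the trial will end with 20 per arm and power 0.69. The document does not support that as an unconditional result, because 20 per arm arises only if nobody is replaced. A reader might also set 20 completers per arm against the pilot studies that the Discussion calls small (at most 21 per group). That is not like for like: Background and rationale shows that 21 per group was the pilot's enrolment and that 10 and 14 patients completed all follow-up.

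The powers above also do not describe every planned analysis. Statistical methods plans last observation carried forward beside the complete-case analysis, and the battery is also given at 3 months, so some patients lost before 12 months would enter the former. Patients lost in the ICU have no battery score to carry forward.

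The defence does not rescue the written derivation. The protocol reaches 80 by rounding up 78, not by dividing 52 by 0.65. The stated minimum of 78 falls marginally short even on the favourable reading. That reading also conflicts with the plan's own sum to 50%. And because patients are allocated after initial consent (Allocation and blinding), those replaced have already been randomised, so the total randomised exceeds 80 and is not stated.

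**Conclusion.** The point holds in this form: the recruited number is wrongly derived (78 where a 50% loss needs 104), the 15% is used twice, and neither the denominator of the 35% nor the total to be randomised is given. The stated power of 0.80 is reached with the planned 80 if replacement is complete and the 35% applies to those discharged (52 completers, 0.81, with no margin). It is 0.77 if the 15% and 35% share a denominator, and 0.69 to 0.74 only if replacement does not take place.

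These figures assume d = 0.8, equal arms, the plan's own loss rates and an unadjusted two-sample comparison of patients with 12-month data. They do not show that the trial is underpowered. They show that its adequacy depends on a choice that the text leaves open.

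**What to change.** Delete the step from 50% dropout to 78 and state one chain with its denominators. If the favourable reading is intended: 52 evaluable; 52/0.65 = 80 retained at ICU discharge, allowing for 35% of those discharged being lost by 12 months; 80/0.85 = 94.1, so about 95 randomised in total (96 for equal arms), allowing for 15% lost in the ICU and replaced. Say plainly that 80 is the number retained, not the number randomised.

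If the 35% is a share of all randomised, either restate the power for 80 retained as 0.77 or raise the number randomised to 104. If replacement will not be done, restate the power for 80 randomised as 0.69 to 0.74. In either case where power falls below 0.80, qualify the adequacy statement in the Discussion.

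Under the favourable reading the cost is a wording change and a matching registry update; no patients are added beyond those that the replacement rule already implies, and about 95 is well within the 300 candidates expected each year in Study setting. Going to 104 would add about 10 patients to the 94 implied now.

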Patients will be constantly monitored during the intervention as part of standard ICU care. This will provide information on changes in mental status, mobility level and physiological parameters (e.g., peripheral oxygen saturation [SpO2], respiratory rate [RR] and heart rate [HR]), allowing the study staff to adapt the interaction, workload and duration of each session to the type of patient profile in real time. Adverse events (e.g., unsafe physiological parameters, unintentional removal of catheters, endotracheal tubes or tracheostomy cannulas) and tolerability issues (e.g., fatigue, extreme sleepiness, confusion) during the intervention will result in interruption or early termination of the session. Interruption or early termination of a session will not preclude participation in subsequent sessions if safety criteria are met (see “Safety and tolerability data” and “Harms and adverse event reporting” for details).

The intervention will be discontinued if patients voluntarily withdraw consent or, if they have not yet been able to give consent themselves, their authorized representative voluntarily withdraws consent, requests to stop receiving the intervention, are transferred to another ICU or die during ICU stay. At the discretion of the clinical staff, the intervention will also be discontinued if there are changes in the patient's medical condition, such as worsening disease, that make continued participation inadvisable or if there are safety concerns that poses a risk to participants. In the event of discontinuation of the intervention, patients will continue to receive standard ICU care. Participants should not participate in other RCT intended to stimulate cognition and provide relaxation during or after the ICU stay.

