### Recruitment

Patients admitted to the ICU will be examined daily during the ICU stay, and, if they meet the eligibility criteria, they or their authorized representative(s) will be contacted for consent. If consent is initially obtained from an authorized representative (e.g., in the case of a comatose, deeply sedated or delirious patient), consent will be ratified once the patient is mentally competent, defined as GCS ≥ 13, RASS between -1 and + 1, and CAM-ICU-7 ≤ 2. Patients who refuse to participate, those whose authorized representatives refuse to participate, and those who refuse to participate even though their authorized representatives have given prior consent will be excluded.

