### Allocation and blinding

After initial consent, patients will be assigned to one of the two study arms using the Research Electronic Data Capture (REDCap) randomization module. A blinded study coordinator, who will not be involved in patient care, intervention, data collection or assessments, will manage this computer-generated procedure. Due to the characteristics of the intervention, neither other study staff nor patients will be blinded. Data collection and assessments will also not be blinded. However, an independent statistician will perform data analysis in a blinded fashion.

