#### Statistical methods

Results will be presented as mean (standard deviation) or frequency (%). Depending on whether the data have a normal distribution, parametric or nonparametric statistics will be used. In case of non-normal data, the median (range) will be reported. To compare results between the RGS-ICU and TAU groups over time, intersubject and intrasubject analyses will be performed, adjusting for multiple comparisons when necessary (e.g., Bonferroni correction). More specifically, intention-to-treat and per protocol analyses will be used. To address missing data, a last observation carried forward analysis together with a complete-case analysis will be performed. Where appropriate, analyses will be controlled for age, sex, delirium, invasive MV, type and dose of pharmacological treatment and/or cognitive reserve (CRQ). Effect sizes will be reported for all significant and non-significant data. Statistical significance will be set at *p* < 0.05. Analyses will be performed using the most recent version of the Statistical Package for the Social Sciences (IBM SPSS Statistics for Windows, Armonk, NY: IBM Corp).

To compare sociodemographic and clinical data between the RGS-ICU and TAU groups, an intersubject analysis will be performed. Intervention characteristics (e.g., session duration, protocols performed, etc.), intervention safety (i.e., number of sessions terminated early due to unsafe events on physiological parameters) and intervention tolerability (e.g., fatigue, extreme sleepiness, confusion) in patients assigned to the RGS-ICU group will be analyzed using descriptive statistics. To compare experienced comfort (PEECE) between the RGS-ICU and TAU groups, an intersubject analysis will be performed. To compare cognition (MoCA, WAIS-IV Forward Digit Span, WAIS-IV Backward Digit Span, RAVLT, TMT, SCWT, FAS, WAIS-IV Digit Symbol-Coding, SDMT and PDQ-5), mental health (GAD-7, PHQ-9 and TOP-8), functionality (WHODAS 2.0) and HRQoL (SF-12) between the RGS-ICU and TAU groups over time, intersubject and intrasubject analyses will be used.

Other analyses will include comparison of changes in the intensity of dyspnea, pain, worry and sadness (VAS) before and after each session in patients assigned to the RGS-ICU group. To this aim, an intrasubject analysis will be used.

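### Replacing randomised ICU dropouts and excluding non-ratifiers after allocation conflicts with the planned intention-to-treat analysis, and the worsening reason may act differently by arm

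*Protocol article*

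**What the plan says.** All references are to the protocol article.

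- **Timing of allocation** (Allocation and blinding): "After initial consent, patients will be assigned to one of the two study arms". Under Recruitment, a representative may give that consent for a patient who is comatose, deeply sedated or delirious, and the patient ratifies it once competent.
- **Non-ratification** (Recruitment): "those who refuse to participate even though their authorized representatives have given prior consent will be excluded".
- **Replacement** (Sample size and power calculation): the reasons given for ICU dropout are "changes in health status that make continued participation inadvisable, mortality in the ICU, transfer to another ICU or withdrawal of consent previously given" by a representative. The section describes such losses as having nothing to do with the study, and then says "these participants, estimated at 15%, will be replaced by new enrolments in a 1:1 ratio".
- **Stopping the intervention** (Experimental condition: RGS-ICU group): at the discretion of clinical staff, "the intervention will also be discontinued if there are changes in the patient's medical condition, such as worsening disease". Standard care then continues. The text does not say whether follow-up visits do.
- **Analysis** (Statistical methods): "More specifically, intention-to-treat and per protocol analyses will be used", and for missing data "a last observation carried forward analysis together with a complete-case analysis will be performed".
- **Outcome timing** (Post-ICU assessments, Table 3): the neuropsychological battery is given at three and 12 months after ICU discharge. The only cognitive test at ICU discharge is the MoCA, which is not part of the composite.

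**The concern.** An intention-to-treat comparison is protected by randomisation because everyone allocated is accounted for in the arm assigned. Here all the replacement reasons, and the refusal to ratify, can arise after allocation. If those patients are swapped out and not followed, the analysed groups are no longer the randomised groups.

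The protocol treats these losses as unrelated to the study. For two of the reasons that is not secure:

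- **Worsening.** The replacement reason closely repeats the rule for discontinuing RGS-ICU sessions. Unblinded staff apply that rule, and the control-condition section has nothing equivalent, since control patients have no sessions to stop.
- **Non-ratification.** Patients are not blinded and can decide whether to ratify knowing their arm.

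If sicker patients, who are likely to have poorer later cognition, leave RGS-ICU more often than control, the 12-month comparison tilts toward RGS-ICU. Blinding the statistician does not help, because the selection happens before analysis.

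**Working it through.** **1. The plan's own figures.** Inputs from Sample size and power calculation: eta squared 0.14, d = 0.8, two-sided alpha 0.05, power 0.80, dropout 50% (15% in the ICU, 35% later).
- d = 2 × √(0.14/0.86) = 0.807, consistent with 0.8.
- A two-sample t-test (noncentral t) gives 26 per arm, 52 in total, with power 0.807. This reproduces.
- The stated 78 reproduces only as 52 × 1.5. Allowing for 50% loss means 52/(1 − 0.50) = 104.
- The planned 80 gives 52 evaluable only if the 15% ICU losses are swapped out and the 35% alone applies: 80 × 0.65 = 52. The power claim therefore rests on the replacement rule.

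**2. How many patients are affected.** 15% of 80 is 12, so 92 are randomised if each is replaced once. If replacements can drop out too, 80/0.85 = 94.1, so 95. Between 12 and 15 randomised patients (12/92 = 13% to 15/95 = 16%) fall outside the 80.

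**3. Whether they reach the analysis.** The first composite value is at three months after ICU discharge. A patient lost in the ICU and not followed has no earlier composite score to carry forward and is not a complete case. The patient is absent from both planned analyses, whatever the analysis set is called.

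**4. Without replacement, still at 80 randomised.**
- Additive 50% loss: 80 × 0.50 = 40, 20 per arm, power 0.69.
- Sequential loss: 80 × 0.85 × 0.65 = 44.2, about 22 per arm, power 0.74.

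**5. Randomised total that keeps 52 evaluable.**
- Sequential: 52/(0.85 × 0.65) = 94.1. Per arm, 26/0.5525 = 47.06, so 48 per arm, 96 in total.
- Additive: 52/0.50 = 104.

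**6. Possible bias (assumed inputs).** The protocol gives no arm-specific loss and no prognosis for those lost. Suppose a share p of one arm is removed, averaging m SD below the rest of that arm, and nothing comparable is removed from the other. The full-arm mean is the mean of the rest minus p × m, so removal shifts the comparison by p × m. The last column is the two-sided rejection rate with no true effect and 26 per arm (noncentral t).

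| p | m (SD) | Bias p × m (SD) | Type I error |
|---|---|---|---|
| 5% | 0.5 | 0.025 | 5.1% |
| 5% | 1 | 0.05 | 5.4% |
| 10% | 1 | 0.10 | 6.4% |
| 15% | 1 | 0.15 | 8.3% |

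The last row is an extreme bound. The 15% in the protocol covers all ICU reasons, including death, and that row puts all of it on one selective mechanism in one arm.

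**The case against.** Three points count against a stronger reading.

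- **Replaced is not the same as excluded.** Only refusals are literally excluded. The other losses are called dropouts and replaced to preserve power, and extra enrolment is compatible with intention-to-treat if the original patients stay in. The discontinuation text does not end follow-up, and the consent section lets data gathered before withdrawal be used unless the patient objects. This stands as far as it goes: a reader might infer that the protocol removes all these patients from the intention-to-treat set, and it does not say so. But it does not say they are followed either, the sample-size arithmetic counts them as lost, and without a post-ICU visit they contribute nothing to the primary outcome.

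- **Loss from the RGS-ICU arm only is not stated.** A reader might infer that the rule strips sicker patients from that arm alone. The reasons are listed without reference to arm, and death, transfer, withdrawn proxy consent and refusal to ratify can occur in either. The text supports an arm-specific mechanism for worsening alone. For non-ratification it supports only that the decision can be made with the arm known.

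- **Some losses are unrecoverable.** Patients who die in the ICU have no 12-month score, and those who withdraw from follow-up cannot be assessed. What can be recovered is the outcome of living patients who stopped sessions or changed ICU and still consent to visits.

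None of this removes the conflict between the replacement rule and the planned intention-to-treat analysis.

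**Conclusion.** The point holds in a limited form. Replacement after randomisation, together with exclusion of non-ratifiers after allocation, conflicts with the intention-to-treat analysis as soon as the replaced patients are not followed, and the protocol makes no provision for following them. About 12 to 15 of 92 to 95 randomised patients are concerned, on the protocol's own 15%.

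Differential removal by arm is a risk, not a stated feature. Its size cannot be derived from the document. On assumed values it runs from 0.025 SD to an extreme 0.15 SD, against a target effect of 0.8 SD, with type I error from about 5.1% to 8.3%. The case for change rests on the analysis population and on the power claim, which depends on replacement; it does not need the upper end of that range.

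**What to change.** Reconcile the sections on the experimental condition, sample size, recruitment and statistical methods as follows.

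1. Delete the replacement rule.
2. Keep every randomised patient in the assigned arm for the intention-to-treat analysis.
3. Seek the three- and 12-month visits from all who are alive and have not withdrawn consent to follow-up, including those who stopped sessions or moved to another ICU.
4. Report ICU deaths and non-ratifications by arm.
5. State whether the 15% and 35% losses are sequential or additive, and fix the randomised total in advance: about 94 to 96 if sequential, 104 if additive. If the total stays at 80, restate power as about 0.69 to 0.74.

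Moving randomisation to the first day a patient qualifies for sessions is not a substitute. Sessions are permitted during delirium, whereas ratification requires a CAM-ICU-7 score of 2 or less, so delirious patients would still be allocated before ratifying. It would also shift the 28-day limit, which is counted from randomisation.

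**Cost:** a protocol amendment and some extra follow-up visits. The sequential total is about what replacement would randomise anyway (92 to 95); the additive total adds roughly ten patients. The study setting section expects 300 candidates a year, so either is plausible.
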